**Participants**							

Blood pressure (Omron HEM-907, average of 4 readings at 2 visits 1 week apart)	**X**		**x**				**x**

Weight	**X**		**x**				**x**

Fasting lipid panel	**X**		**x**				**x**

24-Hour urine collection	**X**		**x**				**x**

Diet (Block food frequency questionnaire)	**X**		**x**				**x**

Physical activity (7-day physical activity recall)	**X**		**x**				**x**

Physical activity (triaxial accelerometer)	**X**		**x**				**x**

Medication adherence (self-reported medication-taking scale)	**X**		**x**				**x**

Psychosocial mediators (SF-36, social support, perceived stress, depression)	**X**		**x**				**x**

Symptom questionnaire	**X**		**x**				**x**

Medication questionnaire	**X**		**x**				**x**

Process measures (patient intervention only: attendance, self-monitoring records)	**X**	**x**	**x**				

### Primary and secondary outcomes

The primary outcome was the change in systolic BP at 6 months. Secondary outcomes included change in diastolic BP, the proportion of participants with adequate BP control at 6 and 18 months, and the effect of treatment on behavior change (i.e., weight loss, dietary pattern, physical activity) at 6 and 18 months. The 6-month outcomes correspond to the maximum impact of the patient intervention but may be too early to reflect maximum impact of the MD intervention. The 18-month outcomes assess the durability of the patient intervention and the cumulative (perhaps maximal) effect of the MD intervention.

### Analysis plan

The data cleaning and analysis stage of the HIP trial has begun. The adequacy of randomization will be assessed by comparing the baseline characteristics of the 4 study groups. Chi-square tests will be used for categorical variables, and the analysis of variance will be used for continuous variables.

For the patient intervention groups only, various measures pertaining to adherence to the patient intervention and its impact on intermediate outcomes will be summarized. For example, for each cohort, the number of intervention sessions attended will be summarized. Similarly, changes in weight, diet, and exercise will be tabulated, and whether the mean changes equal zero will be determined.

For the main analysis of BP changes, results by group and cohort will first be summarized, and then tested for a cohort-by-group interaction. If this interaction is non-significant–suggesting that the intervention effects are similar across cohorts–summary results will be reported but will include cohort as a control variable in all models. For the continuous outcome of systolic BP, the main comparison will be derived from an analysis of covariance model that controls for cohort and baseline systolic BP. The primary hypotheses of interest will be the main effect of the patient intervention, the main effect of the physician intervention, and the patient-by-physician interaction. This last interaction assesses, for example, whether the patient and physician interventions have a separate impact on outcome or, alternatively, whether they act synergistically. For the categorical outcome of percentage of patients at goal, a similar strategy will be followed using logistic regression, and these analyses will also be stratified by whether the patient was at goal at baseline.

The analysis plan accounts for the correlations among the responses for individual patients, these correlations being induced by the nesting of time points within patients within physicians within practices. The analysis of variance paradigm will be used, accounting for the correlations among the 3 time points by separately analyzing the paired scores representing differences between baseline and 6 months and between baseline and 18 months. These comparisons can be preceded by a statistical test, such as Hotelling's T^2^, that takes explicit account of these correlations.

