## Methods and design

### Overview

The HIP study was a nested 2 × 2 randomized controlled trial of a physician intervention, a patient intervention, and both combined (Figure 2). All study procedures were approved by the Duke Institutional Review Board. Recruitment was conducted in waves: i.e., 2 practices were initiated every 6 months to allow adequate time for study personnel to train providers and recruit participants. Each group of practices was considered a cohort (e.g., the first 2 practices recruited are considered Cohort 1). Nesting occurred at the level of the practice and the level of the physician. Primary care practices were randomly assigned to the physician (MD) intervention or to the MD control condition. All participating MDs within a given practice had the same randomization assignment. The MD intervention consisted of training and performance monitoring. Performance data were collected for 18 months, and feedback was provided to physicians every 3 months within that timeframe.

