### Enrollment and randomization of MDs

To avoid contamination among physicians in the same practice, randomization occurred at the level of the practice. Four matched pairs of primary care practices were randomly assigned to physician intervention or control. Practices were matched according to specialty (internal medicine or family practice) and participant mix (percent of participants with Medicaid or Medicare without supplemental insurance). Within each practice, all physicians were invited to participate, with a goal of enrolling 4 physicians at each clinic. All physicians at a given clinic were assigned to the same intervention.

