Near the conclusion of the 6-month follow-up for Cohort 3, the Data Safety Monitoring Board (DSMB) reviewed the study design–in particular, whether it would, in view of the trial's limited budget, be appropriate to reduce the number of cohorts from 5 to 4. This DSMB review included a comparison of the results of the study to date (to which the investigators, with the exception of the study statistician, were blinded) with the assumptions of the power calculations. In approximate numbers, instead of 40% of patients maintaining BP control at baseline, the figure was actually 70%. Moreover, over 95% of the patients who were in BP control at baseline were also in control at 6 months, raising the possibility that using a dichotomous BP control variable as the primary outcome would suffer from a ceiling effect. (Note that such a ceiling effect was not necessarily certain; for example, an effect size of 0.3 could still be generated from a pattern of outcomes centered around 70%, but this preliminary analysis did suggest that patients who were in BP control at baseline were likely to provide less information than desired toward distinguishing the impacts of the interventions.)

In light of these considerations, the DSMB recommended: (a) to reduce the number of cohorts to 4 (to conserve budget); (b) to focus recruitment in Cohort 4 on patients who were not in BP control at baseline (to ensure that the study population approximated the original target population as much as possible); and (c) to change the primary outcome to change in SBP, measured as a continuous variable, while maintaining the dichotomous measure of BP control as a secondary outcome (to increase statistical power by, for example, being able to differentiate between greater decreases in SBP among patients who were in BP control at baseline).

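### For the physician factor, the cohort-by-group test cannot separate practice differences from a varying effect, and the pooled model that follows names no practice-level error

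*Protocol article*

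**What the plan says.** All references are to the protocol article.

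- **Overview.** Practices entered in waves of two, so that "the first 2 practices recruited are considered Cohort 1". Also, "All participating MDs within a given practice had the same randomization assignment".
- **Enrollment and randomization of MDs.** For the physician factor "randomization occurred at the level of the practice", and "Four matched pairs of primary care practices were randomly assigned to physician intervention or control".
- **Content and conduct of the patient intervention.** The closing paragraph gives the enrolled totals: 8 practices (4 per physician arm), 32 physicians and 574 patients.
- **Analysis plan.** For BP change, "results by group and cohort will first be summarized, and then tested for a cohort-by-group interaction". A non-significant interaction is read as a sign that effects are alike over cohorts. Summary results are then reported with cohort kept in every model. The main comparison for systolic BP is an ANCOVA on cohort and baseline systolic BP. The primary hypotheses are the patient main effect, the physician main effect and their interaction. A later paragraph says that correlation from nesting within physicians and practices is accounted for, but the mechanism it goes on to describe is separate analysis of the 6-month and 18-month differences.
- **Sample size and statistical power.** Clustering is assumed to be offset by the gain from covariates. About 340 completers are said to give about 80% power for main effects. The monitoring board later advised "to reduce the number of cohorts to 4 (to conserve budget") and "to focus recruitment in Cohort 4 on patients who were not in BP control at baseline".

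**The concern.** No sentence says outright that a cohort is a matched pair. It follows naturally from two practices per cohort, four pairs, four cohorts and four practices per arm, and from the power section counting the same units as sets of clinics, pairs and cohorts. On that reading each cohort holds one intervention practice and one control practice.

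The physician contrast within a cohort is then a difference between two practices. If that difference varies from cohort to cohort, the reason may be that practices differ or that the physician intervention works better in some places than others. The design cannot tell these apart. A non-significant cohort-by-group test therefore does not show that the physician effect is alike across cohorts.

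The same variation is the natural yardstick for the physician effect, because practices were the units randomized. The named ANCOVA does not use it. If the residual is between patients, the standard error for one of the three primary hypotheses is too small whenever practices differ at all.

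**Working it through.** **1. The plan's own figure.** The power section implies an effect size of 0.3 SD. I assume two-sided 5%, which is not stated.

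- n per arm = 2(1.96 + 0.842)² / 0.3² = 175, or 350 in total, close to the stated 340.
- Power with 170 per arm is 0.79, and 340 / 0.85 = 400 for 15% drop-out.

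The stated figures reproduce as an analysis of independent patients.

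**2. Degrees of freedom.** Eight practices have 7 df: 3 for cohort, 1 for physician arm and 3 left over. Those last 3 are exactly the cohort-by-physician interaction. If the pre-test crosses cohort with all four groups it has 3 × 3 = 9 df, and these 3 are among them.

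**3. Inputs for the error rate.**

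- Patients per practice, m: 574 / 8 ≈ 72 enrolled, or 340 / 8 ≈ 42 at the planned completers.
- Practice ICC (ρ) of the analysed score: not given in the documents; assumed 0 to 0.05.
- No physician effect and no true heterogeneity; residual error between patients.

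**4. Formula.** With total variance 1, a practice mean has variance ρ + (1 − ρ)/m, while patient-level error allows only (1 − ρ)/m. The ratio is λ = 1 + mρ/(1 − ρ). It multiplies both the physician F and the cohort-by-physician F. Type I error of the physician test ≈ 2{1 − Φ(1.96/√λ)}.

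Example, m = 72 and ρ = 0.02: λ = 1 + 72 × 0.02/0.98 = 2.47; 1.96/√2.47 = 1.25; type I error ≈ 0.212.

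**5. Results** (simulation, 200,000 trials per row):

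| m | ICC | λ | Type I, formula | Type I, no pre-test | Type I after passed 3-df pre-test | 3-df pre-test significant | 9-df pre-test significant |
|---|---|---|---|---|---|---|---|
| 72 | 0 | 1.00 | 0.050 | 0.050 | 0.050 | 0.050 | 0.049 |
| 72 | 0.01 | 1.73 | 0.136 | 0.135 | 0.135 | 0.209 | 0.139 |
| 72 | 0.02 | 2.47 | 0.212 | 0.210 | 0.211 | 0.365 | 0.250 |
| 72 | 0.05 | 4.79 | 0.370 | 0.364 | 0.369 | 0.652 | 0.522 |
| 42 | 0 | 1.00 | 0.050 | 0.051 | 0.051 | 0.050 | 0.050 |
| 42 | 0.01 | 1.42 | 0.101 | 0.099 | 0.099 | 0.137 | 0.096 |
| 42 | 0.02 | 1.86 | 0.150 | 0.148 | 0.149 | 0.236 | 0.156 |
| 42 | 0.05 | 3.21 | 0.274 | 0.268 | 0.270 | 0.485 | 0.351 |

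The two type I columns with and without the pre-test agree because the mean of the four pair differences and their spread about that mean are independent in a balanced design. A small spread says almost nothing about whether the mean is too far from zero.

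**6. Analysis at the randomized unit.** A paired t-test on the four within-cohort practice differences (3 df) keeps type I error at 0.049 to 0.051 throughout. Its power for 0.3 SD at ICC 0, 0.01, 0.02 and 0.05 is 0.68, 0.47, 0.36 and 0.22 with m = 72, and 0.47, 0.37, 0.30 and 0.20 with m = 42.

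**The case against.** The strongest reply is that the inflation does not come from the pre-test. The table confirms this: a reader might infer that the gate damages the error rate, or that the plan offers it as protection, and neither is supported. The cause is the missing practice-level error, and dropping the gate alone would leave the physician error rate where it is.

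Next, the article says nesting within practices is accounted for, and a condensed article may leave the variance model to a fuller document. That is fair, and if practice-level error is used the inflated rates disappear. But the mechanism the article gives deals with repeated time points, and its ANCOVA is specified by cohort and baseline systolic BP only. Even on the generous reading, the error term would do the protecting, and the test would still not show that the physician effect is alike across cohorts.

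Three further inferences go too far.

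- The interaction is not purely a test of practice differences. It mixes them with any real heterogeneity of the physician effect.
- It does not follow that a significant test leaves no summary result. The article is silent on that branch, and the sentence on the ANCOVA carries no condition.
- The recruitment focus in Cohort 4 does not build in differing effects. It shifts baseline BP, which the model adjusts for. Differing effects are plausible, since the power section says controlled patients tell less about the interventions, but they are not certain.

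The ICC is also an assumption. At zero there is no inflation, and matching and baseline adjustment may keep it small.

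**Conclusion.** The point stands for the physician main effect, one of three primary hypotheses. Taking a cohort as a matched pair, the article draws a conclusion from the cohort-by-group test that the design cannot support, and the pooled model it names has no stated practice-level error. How far the error rate departs from 5% depends on an ICC the documents do not give and on the residual being between patients. At ICCs of 0.01 to 0.05 it is roughly two to seven times nominal across the two practice sizes considered, and a passed pre-test changes this by no more than simulation noise or a few tenths of a percentage point.

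The patient-intervention effect is not touched. Patients were randomized within clinic, so a shift common to a practice cancels from that comparison. The arithmetic behind the 340 and 400 patients is not in dispute, but it treats patients as independent and does not carry over to a factor assigned to eight practices.

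**What to change.** - Do not let the cohort-by-group test decide whether results are pooled. Always report the pooled estimates with cohort in the model.
- Test the physician effect against practice-within-cohort variation: either a random practice term with small-sample degrees of freedom, or the 3-df cohort-by-physician mean square as the error term. State which.
- Show physician and patient estimates by cohort as description.
- Limit heterogeneity testing to cohort by patient intervention, read alongside baseline systolic BP because of the change in Cohort 4 recruitment.
- Withdraw the claim of about 80% power for the physician main effect.
- Record the change before the physician comparison is run, since the article says analysis has begun.

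The work is a change of wording and model, with no new data. The cost is more than a lost p-value: the physician test has 3 error degrees of freedom, a wider interval and the lower power shown in step 6 of the working. That is the precision eight randomized practices can give.

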At the first screening visit, the consent form was reviewed and signed, height, weight and BP were measured, and body mass index (BMI) was calculated. A self-administered medical history questionnaire was used to establish the final set of eligibility criteria. At a second screening visit, questionnaires and interviews established the patient's commitment and ability to participate, and a fasting blood specimen, 24-hour urine collection, and a second BP measurement were obtained. Participant baseline characteristics are shown in Table 2.

**Table 2 T2:** Baseline patient characteristics (N = 574)

**Characteristic**	**%***
N	574

Age, mean years (SD)	60.5 (11.4)

Female sex	61

Completed high school	93

Adequate income (self-reported)	85

African-American race	37

Medical history	

Taking BP medications	95

Ever smoked	48

Physical activity (accelerometry), mean minutes/week (SD)	34 (106)

Diabetes	30

Hyperlipidemia	48

* Unless otherwise indicated.

BP = blood pressure; SD = standard deviation.

After eligibility was established, randomization occurred using a computer-generated algorithm, stratified by cohort and by clinic. Participants were randomized in varying block sizes to ensure comparable numbers of participants in each assignment over time. Each participant learned of his/her treatment assignment from a HIP staff member who was not involved in collecting study measurements. Intervention staff members then instructed participants on the details of their assigned intervention.

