The CHAs served as familiar, non-authoritative resources for study participants, strengthening communication between the research group and the participants and providing additional social support. The intent is that the CHAs will have sufficient knowledge and skills to serve as ongoing resources in their communities and to help sustain the effects of the project after it is completed.

The outcomes were measured at the level of the patient, who was exposed to neither intervention, MD intervention alone, patient intervention alone, or both interventions. Overall, 8 practices (4 per treatment group), 32 physicians (4 per practice; 16 per treatment group), and 574 patients (289 control and 285 intervention) were enrolled (Figure 2).

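### The plan says it allows for nesting in practices, but the named model gives the practice-randomised physician effect no practice-level error term, so run as written its type I error exceeds 5% unless the ICC is near zero

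*Protocol article*

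**What the plan says.** All references are to the protocol article.

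- **Unit of randomisation** (Enrollment and randomization of MDs): "To avoid contamination among physicians in the same practice, randomization occurred at the level of the practice". The same section adds: "Four matched pairs of primary care practices were randomly assigned to physician intervention or control".
- **Cohorts** (Overview): "Each group of practices was considered a cohort (e.g., the first 2 practices recruited are considered Cohort 1". With four pairs and four cohorts of two practices, a cohort is very probably a matched pair. That is my inference; the article does not say so.
- **Size** (Active intervention: structure and content): "8 practices (4 per treatment group), 32 physicians (4 per practice; 16 per treatment group), and 574 patients (289 control and 285 intervention) were enrolled".
- **Patient randomisation** (Enrollment and randomization of patients): "randomization occurred using a computer-generated algorithm, stratified by cohort and by clinic".
- **Primary model** (Analysis plan): "the main comparison will be derived from an analysis of covariance model that controls for cohort and baseline systolic BP". Its primary hypotheses are the patient main effect, the physician main effect and their interaction. A cohort-by-group interaction is tested first.
- **Correlation** (Analysis plan): the section states that the plan allows for correlation arising from nesting in patients, physicians and practices. The method it then describes is "accounting for the correlations among the 3 time points by separately analyzing the paired scores representing differences", for baseline to 6 months and baseline to 18 months, optionally preceded by a test such as Hotelling's T-squared.
- **Clustering in the power section** (Sample size and statistical power): clustering is said to lower power and is assumed roughly to cancel the gain from covariates. No ICC is given. A sign test over practice pairs appears there only as an argument for five pairs.

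**The concern.** What the plan says it does and what it names do not match. Differencing a patient's own measurements removes correlation within that patient over time. It does nothing about two patients of the same practice resembling each other in their change in BP.

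Adjusting for cohort does not close the gap. If a cohort is a matched pair, the cohort term removes differences between pairs. The difference between the two practices of a pair remains, and it is completely confounded with physician arm. An ordinary ANCOVA judges that difference against the scatter between patients, when the relevant yardstick is the scatter between practices.

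The result for the physician arm is a standard error that is too small, residual degrees of freedom in the hundreds where the design supports about 3, and a p-value that is too small. The Background says that health care organisations should use the trial to decide whether to adopt one or both interventions, so the two effects need equally trustworthy error rates.

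**Working it through.** **Inputs from the article.** 8 practices in 4 pairs; 574 patients, so 574/8 = 71.75 enrolled per practice; 340 completers planned from 400 enrolled, so 340/400 = 85% retention and 574 × 0.85/8 ≈ 61 completers per practice. An effect size of 0.3 is implied in the power section.

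**Assumed, not in the article.** Two-sided 5% test; ICC from 0 to 0.05; clustering by practice only, with no further physician-level correlation.

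**1. The plan's own figure.** For 170 patients per arm and 0.3 SD: 0.3 × √(170/2) = 2.766, and Φ(2.766 − 1.96) = 79.0%. This matches the stated power of about 80%, so that figure is for independent patients.

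**2. Type I error of the physician test without a practice term.** Design effect DE = 1 + (m − 1) × ICC. Actual type I error = 2 × [1 − Φ(1.96/√DE)].

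| ICC | DE, m = 61 | Type I error | DE, m = 71.75 | Type I error |
|---|---|---|---|---|
| 0 | 1.0 | 5% | 1.0 | 5% |
| 0.01 | 1.6 | 12% | 1.7 | 13% |
| 0.02 | 2.2 | 19% | 2.4 | 21% |
| 0.05 | 4.0 | 33% | 4.5 | 36% |

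**3. Simulation of the stated ANCOVA** (4 cohorts of 2 practices, no physician effect, 4,000 replicates per ICC).

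| ICC | 61 per practice | 72 per practice |
|---|---|---|
| 0 | 5.8% | 4.1% |
| 0.01 | 14.1% | 13.9% |
| 0.02 | 23.5% | 20.9% |
| 0.05 | 38.6% | 36.9% |

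In the 72-per-practice runs the ICC is that of the residual after baseline adjustment. The 61-per-practice results exceed the formula mainly because of how baseline acts. If baseline (correlation 0.5) explains variance between patients but none between practices, an ICC of 0.01 becomes 0.01/(0.01 + 0.75 × 0.99) = 0.0133 after adjustment. The formula then gives 14%, 22% and 38% at ICC 0.01, 0.02 and 0.05. That choice enlarges the problem somewhat, so the formula values are the more cautious end of the range.

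**4. The cohort-by-group pre-test.** Taken as cohort by physician arm in the 72-per-practice simulation, it was non-significant in 79%, 63% and 35% of trials at ICC 0.01, 0.02 and 0.05. Among those trials the physician test still rejected in 14%, 21% and 38%.

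**5. What holds its level.** A paired t-test on the four within-pair differences of adjusted practice means (3 df) rejected in 4.3–5.3% in one simulation and 4.5–5.2% in the other. The patient main effect under the stated ANCOVA rejected in 4.2–5.1%.

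**6. ICC implied by the plan's offset assumption.** If clustering just cancels the covariate gain, DE = 1/(1 − R²). With 340/8 = 42.5 completers per practice, ICC = [1/(1 − R²) − 1]/41.5. This gives 0.008 at R² = 0.25 and 0.024 at R² = 0.5 (both R² values assumed). At 61 patients per practice the formula in step 2 then gives 11% and 21%.

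**7. Price of a valid test.** Ratio of confidence interval widths = √DE × 3.182/1.96. With m = 71.75 this is 2.1, 2.5 and 3.5 at ICC 0.01, 0.02 and 0.05. Power for 0.3 SD on 3 df with 574 patients is 47%, 36% and 22% without covariate gain, and 73%, 60% and 38% with R² = 0.5.

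**The case against.** The article condenses a fuller plan that is not shown. The sentence naming the ANCOVA lists covariates and does not describe the error structure. The section states that nesting is allowed for, and the power section says that clustering costs power, which is true of a valid test only if the analysis allows for it. The error term may therefore be written down elsewhere, and the inflation depends on an ICC that the article does not give.

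Part of this stands. A reader might infer that the trial will ignore clustering. The article does not show that: a practice term is not ruled out. A reader might also infer that the plan claims differencing deals with practices. It does not: differencing is tied explicitly to the three time points. Nor do the figures support saying that a false positive is likely, since every rate computed is below one half and at ICC 0 the test holds its level.

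The objection does not dispose of the point. The article fixes the model, its covariates, its hypotheses and its device for correlation, and none of these supplies a practice-level error term. An ICC of essentially zero also sits badly with the plan's own premise that clustering costs about as much as the covariates gain. The sign test is no fallback: with the four pairs run, its best possible result is p = 0.0625 one-sided or 0.125 two-sided.

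**Conclusion.** The point holds for the physician main effect. The statement on nesting is not matched by any named method, and running the named model would give that test a type I error of about 12–14% at ICC 0.01, 19–24% at 0.02 and 33–39% at 0.05. Only with an ICC near zero is it about 5%. These sizes rest on an assumed ICC, 61 to 72 patients per practice and clustering by practice alone.

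It would be tempting to extend the criticism to the patient intervention, which the same model tests without clinic. The simulations do not support that: its error rate stayed at about 5%, because patients were randomised within clinic. Leaving clinic out can cost that effect a little precision but does not make it anti-conservative.

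This should be settled before the physician effect is analysed, because it determines the validity of a primary test.

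**What to change.** - **Physician main effect:** name the practice-level error term. One option is a linear mixed model with random practice (and random physician), cohort and baseline systolic BP as fixed effects, and Kenward-Roger or Satterthwaite degrees of freedom. Another is a paired analysis of the four within-pair differences in baseline-adjusted practice means, on 3 df. The two need not give identical results, so one should be named as primary.
- **BP control at goal:** use a matching cluster-aware method in place of plain logistic regression for the physician effect.
- **Nesting statement:** say which named method covers practices and physicians, and which covers time points.
- **Optional:** include clinic when estimating the patient effect, since that randomisation was stratified by clinic.

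The cost is a change of wording and of model, with no new data. The loss of precision is real: roughly 2 to 3.5 times wider intervals for the physician effect at ICC 0.01 to 0.05, with power well below the stated 80% (step 7). Reports should therefore not read a non-significant physician effect as evidence of no effect.
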